**Visual Abstract**

Using a participatory action research approach,1 we co-created the Self-Management for Amputee Rehabilitation using Technology (SMART) web-based app to guide adults with Lower Limb Amputation (LLA) to actively engage in self-management. In the current proposed study, we will use a Type 1 Effectiveness-Implementation Hybrid Design2 randomized controlled trial (RCT) to evaluate the 6-week effectiveness of SMART on patient-relevant outcomes, while documenting implementation factors.

**
[figure not shown]
**

Figure 1: Visual Abstract for SMART Proposal

**1. THE NEED FOR A TRIAL**

**1.1 Problem:**Amputation of the lower limb (LLA) can be devastating. At the individual level it reduces physical, emotional, and social wellbeing; while contributing to a significant burden on the healthcare system. In 2017, Imam and Nominated Principal Applicant (NPA) **[name]** et al., reported that 7,300 Canadians have a LLA each year-- mostly (85%) occurring in >50 years of age.3 The primary cause of LLA was related to diabetes and vascular complications (91%),3 and most (~70%) LLA occurred in men.3 For many patients, undergoing an LLA predicts poor health outcomes.4 Women are more likely to be readmitted to hospital compared to men, due to complications after LLA,4 because of greater risk of morbidity and mortality after LLA including a higher risk for falls.5-7 Women also experience more psychological and social challenges,8-10 including a lack of confidence,7, 11 fear of falling,7, 12 depression7, 13 and pain.8 Combined or alone, these factors create critical barriers to independence in daily tasks (e.g., toileting) and engagement in social activities (e.g., meeting friends, volunteering).7 Taken together, LLA is a significant life event, that requires a wholistic approach during recovery to address both physical and psychological barriers post LLA to maximize a person’s autonomy and quality of life. Additionally, the COVID-19 pandemic has impacted the delivery and accessibility of healthcare services.

Canadian cost estimates of LLA are not available, but the projected lifetime cost of an LLA per person was estimated (in 2002) at US $509,000.14 The cumulative

national hospital costs associated with amputation was estimated to be more than $8.3 billion at US in 2009.15 In addition, the total cost for care for diabetes related LLA for 3,400 patients was exceeded $206 million in 2012 US.16 In the United Kingdom, the economic burden associated with diabetes-related amputations was £43.8 million for inpatient care.17 The cost for post amputation care (i.e., prosthetic care, physical therapy, transport, wheelchair use) was £20.8 million at United Kingdom.17 In Canada, there is more reliance on outpatient rehab due to high inpatient costs: 37 days is the average length of stay for an inpatient program.18 Despite evidence inpatient rehab is superior to outpatient,19 Imam and **NPA** **[name]** et al., found that only 18% of adults with LLA received inpatient rehab in Canada,18 and rehab for majority of patients was reliant on outpatient services. This is especially concerning as rehab services are more available in urban than remote regions.20, 21 As LLA affects a significant number of Canadians, and given the current trend for rehab services to be provided outside of the inpatient setting, coupled with the COVID-19 pandemic, new delivery strategies are urgently needed.

Self-management is defined as the provision of education and supportive interventions to increase patients’ coping skills and build confidence to better manage disease-related physical and psychological challenges.22, 23 Delivery of self-management programs through home computers, smart phones or tablets (eHealth),24 is emerging as an important option to deliver and manage health conditions in the community-setting, particularly during COVID-19. In general, tailored self-management programs, using feedback and peer support,25, 26 are effective interventions in other chronic conditions (such as diabetes). These interventions

also show effectiveness when delivered via eHealth.25 Specifically after LLA, education and skill development can support the recovery process, especially for older adults.27 However, to date, based on our review of the published evidence, there are only five publications28-32 using telehealth with people after LLA, and only one face-to-face study33 which tested effectiveness of self-management interventions after LLA. That is, we could not identify any published eHealth interventions using self-management for adults with LLA. Given the number of Canadians with a LLA each year, the declining emphasis on inpatient rehab, it is imperative to work with key stakeholders to develop an test acceptable and feasible rehab options. eHealth solutions post LLA have the potential to increase access and improve health outcomes,27, 33 but we need Canadian data before this delivery mode can be integrated into clinical practice. We completed foundation work with stakeholders (e.g., adults with LLA, clinicians, community organizations, etc.) to develop and test feasibility for an eHealth intervention34-36 called **S**elf-**M**anagement for **A**mputees using **R**ehabilitation **T**echnology (SMART) that is ready to test effectiveness, and describe key implementation factors for future integration into clinical practice, if appropriate.

**1.2. Principal research questions:** We will use a Type 1 Effectiveness-Implementation Hybrid Design2 randomized controlled trial (RCT) to evaluate the 6-week effectiveness (and 4-week retention effect) of SMART on patient-relevant outcomes, while documenting implementation factors. Please note, we chose the primary (and secondary) outcomes based on feedback from adults with LLA who identified walking (e.g., mobility) and new identity as of great importance in the recovery process. Our research questions are:

**Q1.** What is the effect of SMART on walking confidence and capacity in adults aged over 50 years with a LLA?

**Q2.** What is the effect of SMART on physical activity identity, knowledge, self-efficacy, and falls confidence in adults aged over 50 years with a LLA?

**Q3.** What are the essential factors required to implement SMART into clinical practice?

We hypothesize that older adults with LLA who receive usual care and the SMART intervention, compared with usual care, paper-based education, and social visits (control group intervention) will have greater positive change in:

**H1.** walking capacity, operationalized as higher change score with the two-minute walk test;37

**H2.** physical activity identity, knowledge, self-efficacy, and falls confidence, operationalized as higher change score with the physical activity identity questionnaire,38 patient activation measure,39 and activities specific balance confidence scale.40

**Work completed to support this proposal:**We have completed a number of key feasibility and development studies to support this next phase of testing effectiveness of the innovation (SMART eHealth intervention) and describing its implementation. Using a participatory action research approach,1 we created a Steering Group with our clinical co-investigators (Co-applicants (Co-A) clinicians **[name], [name], [name] and [name]** and patient partners **[name], [name], [name])**. We met 8 times over two years. We co-created the SMART web-based app (please see **Appendix A**), designed to guide adults with LLA to actively engage in self-management. The app is asynchronously monitored through a website portal. There were 31 clinicians, and 26 adults with LLA (73% men) who engaged in semi-structured interviews to identify common themes in the recovery process, and app content to best augment existing LLA rehab. Key findings were: adults with LLA (i) requested tools and strategies to return to walking and independence in activities of daily living (ADLs); and (ii) perceived a new identity after amputation. This feedback was incorporated into the SMART intervention, for required content and the need for peer support to enact the principles of self-management.34, 36 In parallel, we conducted a systematic review and meta-analysis of telehealth interventions for patients with lower limb musculoskeletal surgery41 to identify effective behavior change techniques (BCTs)42, 43 to incorporate into SMART. Self-efficacy44 and action planning theory45 informed the development of SMART. We were also guided by the Theoretical Domains Framework46, 47 to incorporate relevant BCTs within SMART. For example, social support, instruction on how to perform the behavior, self-monitoring behavior, etc. We currently completing a pilot study with a mixed method approach to address design and SMART intervention fidelity with 10 participants who have lived with a LLA for at least 1 year.48

**1.3 Why the trial is needed now:** Self-management programs reduce the number and length of hospitalizations in a variety of chronic disease conditions;49 subsequently reducing health risks, restoring function and independence, and promoting quality of life.49 On-line health education is lauded for being interactive and enabling older adult learners to re-engage over sustained periods, at their own convenience,50 while improving quality of care51 and facilitating adherence to treatment.24 eHealth enhances communication between patients and health care providers,52 and reduces costs while increasing access to health care and evidence-based health information. eHealth initiatives also offer an avenue for continued service delivery during the COVID-19 pandemic. However, to date, only one self-management program (published in 2009) was developed and evaluated for adults with LLA.33 The program, while promising, had a number of important limitations including: i) no involvement of trained peer facilitators [involving peers (e.g., social support) which is critical in the success of self-management programs53]; ii) missing knowledge content such as prosthetic and residual limb management, physical activity, and weight control: all identified as critical factors in our exploratory study34, 36 and in the literature54; and iii) face-to-face program delivery, which limits accessibility to programs to people who live in close proximity or are mobile enough to attend. Therefore, online approaches may offer greater access to self-management for people with LLA. We co-designed SMART an eHealth intervention to augment current rehabilitation and improve outcomes for people with LLA. The time is right now to conduct this trial given (i) our substantial ground work in this area; (ii) the number of people with LLA; (iii) the reduction in available inpatient rehab options; (iv) the widespread access of the internet by adults and older adults (in BC, 86% of adults 45-64 years and 55% >65 years have access to internet at home use55), and (v) a significant healthcare cost associated with LLA (*Section 1.1*).14-17

**1.4 How the results will be used:** Currently adults with LLA receive fewer hours of rehab than is considered best practice, and limited management post-discharge.18 This reduction in care creates a gap in the consolidation of skills and understanding, potentially leading to decreased mobility, functional independence, quality of life,19, 56 and a significant healthcare cost.14-17 SMART has the potential to address the gap and improve LLA outcomes. Our study will enable us to assess the clinical effectiveness, and key implementation factors, of SMART with a sample of people with LLA, with attention given to sex, gender and cause of amputation. In sum, it will provide essential information for integration of SMART into clinical practice, if appropriate.2 This study will provide us with a better understanding of the effects of SMART on walking capacity and relevant outcomes, while observing and gathering information on implementation of SMART in two provinces (BC and ON).

Beyond the potential for scale up and spread of SMART as a clinical innovation, we anticipate the results will be of interest to clinicians locally and nationally. As eHealth is relatively new as an intervention in clinical practice beyond post-amputation, we anticipate our methods will be of interest to other clinical areas. We also anticipate the findings from this study will provide valuable information on service provision via eHealth during the COVID-19 pandemic. Therefore, for our end-of-grant KT strategies we will disseminate findings via websites (e.g., health authorities in BC and ON), electronic and print newsletters (e.g., Physiotherapy Association of BC and ON), blogs, present at provincial practice forums, national webinars, and through social media (e.g., Twitter). We will build on our existing partnerships to reach members of relevant associations, such as the International Society of Prosthetics and Orthotics Canada, and provide summaries for their websites and electronic newsletters. We will submit abstracts to international conferences (e.g., International Society of Prosthetics and Orthotics World Congress), and manuscripts will be submitted for publication. We will work with our patient partners to share plain language summaries with other adults with LLA via newsletters, social media and websites (e.g. Amputee Coalition of BC).

**1.5 Possible risks associated with trial:** Based on our systematic review of telehealth interventions for people with LLA, the risk is minimum. In addition, based on our preliminary findings of the pilot work, risks associated with SMART is minimum. The preliminary results showed the promising quality of content as well as the acceptability of study protocol and assessments. The SMART content incorporates extensive safety-related material, including the identification of risks and avoiding unsafe situations (e.g., identification of potential skin breakdown on the residual limb, falls). Also, all participants can contact the group trainer (SMART or control group trainer) or the study coordinators immediately if they experience unusual discomfort, pain or physical symptoms. Additionally, participants can discuss the issues with care providers. Conducting this study is critical to explore issues, such as over exertion or residual limb skin breakdown due to promotion of physical activity.57 It is also possible that participants could experience altered emotional status from not meeting goals.58

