**Control Intervention:**Participants in the control arm will receive usual care after LLA, education, and social calls. The education booklet is typically offered to patients at discharge, and includes information about LLA consequences, adjusting to amputation, pain management, limb positioning and exercises, mobility (e.g., wheelchair safety, hopping, and transfers), residual limb management (e.g., skin care and diabetic foot care), tips for preparing the home, and driving. A single weekly structured email or telephone contact (based on preferences, n=6 in total) will be made by the trainer. The purpose of the contact is to answer any questions, and to help control for attention bias.45

**2.3 Allocation - Sequence Generation and Randomization:**We will use a central computerized randomization process with variable block sizes to randomly allocate the participants to the intervention (SMART) group or control group using a 1:1 ratio by an independent statistician.

An independent statistician will provide the randomization list through REDCap (REDCap Software, Vanderbilt University and National Institute of Health, USA). The research coordinator will obtain written informed consent (Over Qualtrics platform) and a blinded assessor will complete the baseline assessment. The research coordinator will meet with the participant over Zoom (a secure, UBC-based platform) to guide them through the consent form and answer any questions. At the completion of baseline assessment, the research coordinator will log onto the system to determine the next allocation. The research coordinator will work with the group trainers to set up an appointment. Our protocol for all participants is to complete the baseline assessment, randomization and training within two weeks.

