**2.4 Protecting against bias - Blinding:**Blinding of participants for the RCTs on the effect of eHealth interventions is impossible because of nature of intervetnions.66 Therefore, it is difficult to blind participants to the intervention received. The assessors will be blinded to group allocation, we will complete the primary outcome (TUG and ASCQ) first, and participants will be asked not to disclose their group allocation during assessments.66 Furthermore, we will have separate trainers for each group (to minimize trainer bias); and the primary outcome measure, the TUG is a performance-based measure with standardized instructions. Finally, all statistical analyses will be conducted by a blinded statistician.

**2.5 Inclusion and Exclusion Criteria:**To be included, participants will: have a unilateral dysvascular- or diabetic- related LLA (transtibial or transfemoral);3have conducted the casting for their initial prosthetic limb (up to 2 years); be aged ≥ 50 years (85% of adults with LLA);3 have a computer or tablet and have access to the internet, and self-identify as being able to speak and read English. We will exclude adults with substantial health conditions (e.g., congestive heart failure, diagnosed dementia); those anticipating further surgery (e.g. LLA revision) as identified by our study sites’ physiatrists; and an ability to use a tablet (e.g./ using hands for typing). Given these criteria, the results of this study will not be generalizable to all adults with LLA such as the very young and those who do not speak English. As most people with LLA are >50 years old and more than 90% of the population of BC and ON speak English, we are confident of obtaining a representative sample.

**2.6 Duration of Intervention:**Participants in the SMART group will receive the intervention for six weeks. Participants in the control group will be contacted weekly for a similar 6 week period.

**2.7** **Frequency and Duration of Follow-up:**There are six weekly SMART modules with each taking approximately 20 to 30 minutes to complete. Individuals will be encouraged to complete one module a week to reduce any perceived burden, and gradually integrate the information. Participants from both groups will receive a weekly contact: SMART group participants will receive a 20 minute telephone call/Zoom video call from peers, and the Control group participants one email or phone call by trainer.

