| What (materials) | Participants in SMART group will have access to the SMART platform for 10 weeks. SMART includes 6 modules, about 20 to 30 minutes in length, about the self-regulatory skills, managing mental wellness, physical health, residual limb management, managing a prosthesis, and managing daily living activities. Participants will receive a weekly 20-minute telephone contact from peers for 6 weeks to facilitate motivation using goal setting and action planning. There is also a *resource icon* that provides more information and resources, such as timeline after LLA, and funding for prostheses. |
| What (Procedures) | It is a multi-site parallel RCT at BC (Vancouver Costal Health, Fraser Health, Interior Health, Northern Health, and Vancouver Island Health), Toronto, ON (West Park Healthcare Centre & Sunnybrook Health Sciences Centre), and London, ON (Parkwood Hospital). The research coordinator will provide the contact information for each participant, to his or her trainer. The subjects in SMART group will receive online training on using the online SMART platform. An additional icon in SMART enables direct *private email contact to the trainer,* so that participant questions or problems are quickly addressed. The trainer will be a registered physiotherapist (PT) or occupational therapist (OT) with more than 5 years clinical experience who will arrange the first telephone call of peers. If there is also no online activity within one week through SMART by subjects, the trainer will call the subject to foster motivation and troubleshoot the potential technical problems. |

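### Over-exertion and residual-limb skin breakdown, named as critical to explore, have no scheduled, identical ascertainment in the two arms in the text shown

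*Protocol*

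**What the plan says.** Protocol section 1.5 gives a safety purpose for the trial: "Conducting this study is critical to explore issues, such as over exertion or residual limb skin breakdown due to promotion of physical activity". It also names falls and skin breakdown among the unsafe situations that the SMART content covers. For reporting, it says that "all participants can contact the group trainer (SMART or control group trainer) or the study coordinators immediately if they experience unusual discomfort", and that participants may also raise problems with their care providers.

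Section 2.7 sets out what each arm is given every week: "SMART group participants will receive a 20 minute telephone call/Zoom video call from peers, and the Control group participants one email or phone call". Under Control Intervention in section 2.2, the control contact is "A single weekly structured email or telephone contact" made by the trainer, and "The purpose of the contact is to answer any questions, and to help control for attention bias". Section 2.4 provides a different trainer for each arm.

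SMART participants also have portal monitoring with a trainer contact after seven inactive days (section 2.2, Delivery), and a private email icon to the trainer (Appendix B). Twenty of them are interviewed at T3, partly about perceived disadvantages of the programme (section 2.8, Implementation).

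**The concern.** The protocol names two harms as critical to explore but, in the text shown, sets up no measurement of them. If their occurrence is known only when a participant volunteers it, the count in each arm depends on how often, how easily and to whom participants in that arm speak. Those conditions differ by design. A difference in counts could then reflect reporting, and similar counts could hide a real difference. Analysis cannot repair this later, because an analysis plan cannot use data that were never collected. What is at stake is the descriptive safety information from a trial that promotes physical activity after amputation. The primary comparison is not at stake.

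**Working it through.** The protocol gives no harm rate, capture probability or harms sample size, so there is no stated figure to reproduce on this point. The check is mainly a comparison of sections.

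**Step 1. Is either harm measured on a schedule?** I went through section 2.8 item by item.
- TUG and ASCQ measure mobility and walking confidence.
- ABC measures balance confidence. It does not count falls.
- The action-planning and habit scales ask about skin monitoring. They show whether a person plans or habitually makes the check, but not whether the skin broke down.
- The pain VAS covers residual-limb pain, phantom pain and phantom sensation over the past week. Pain is neither skin breakdown nor over-exertion, and a one-week window at T2 misses most of the six-week intervention.
- CES-D covers mood over the past week. SMFA items 1 to 34 cover function.
- Encounters with rehabilitation providers and surgical consultations are collected over the six weeks. No reason for the encounter is specified, and the four-week retention period is not covered.

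Result: no item records over-exertion, residual-limb skin breakdown or falls.

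**Step 2. Are the routes for spontaneous report the same in both arms?**

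| Route | SMART | Control |
| --- | --- | --- |
| Weekly scheduled contact | 20-minute call from a peer | one email or call from the trainer |
| Portal monitoring, seven-day inactivity contact | yes | no |
| Email icon to the trainer inside the platform | yes | no |
| T3 interview including disadvantages | 20 participants | none |
| Own arm's trainer, on the participant's initiative | yes | yes |
| Study coordinators, on the participant's initiative | yes | yes |
| Coordinator contact every 4 weeks (section 2.14) | yes | yes |

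The last three rows are common to both arms. The coordinator contact falls about twice in the (6 + 4) = 10 weeks of intervention and retention, since 10/4 = 2.5. Its stated purpose is to limit loss to follow-up, and no harms question is described for it.

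**Step 3. What does unequal capture do?** Let the true risks be r_S and r_C and the probabilities that an event is reported be d_S and d_C. The observed ratio is (r_S/r_C) × (d_S/d_C). It equals the true ratio only if d_S = d_C. The protocol gives no basis for either d, so the factor cannot be given a value, and it may lie on either side of 1.

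**Step 4. Which way would it go?** The amount of contact is greater in SMART, and SMART content teaches recognition of skin breakdown. However, the trainer is one of the two reporting contacts named in section 1.5, and it is the control participant who hears from a trainer every week. The SMART weekly call comes from a peer and concerns goals, progress and support. The control booklet also covers residual-limb skin care. The direction is not settled by the text.

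**Step 5. What could equal capture achieve at this sample size?** Section 2.10 gives 34 per arm evaluable and 41 per arm recruited. The 34 reproduces: 2 × (1.96 + 0.84)² × 19.9² / 13.6² = 33.6, rounded up. For two proportions, with p̄ their mean, power = Φ{[|p1 − p2| − 1.96√(2p̄(1 − p̄)/n)] / √([p1(1 − p1) + p2(1 − p2)]/n)}. The event rates below are assumptions, since the protocol gives none.

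| Assumed risks | Power, 34 per arm | Power, 41 per arm |
| --- | --- | --- |
| 10% v 20% | 21% | 24% |
| 10% v 30% | 54% | 62% |
| 20% v 40% | 44% | 51% |

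For the first row at 34 per arm: (0.10 − 1.96 × 0.0866)/0.0857 = −0.81, and Φ(−0.81) = 0.21. Even complete and equal capture would support description rather than a formal test.

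**The case against.** The strongest reply is that part of the protocol is missing. Section 2.17 cites a Data and Safety Monitoring Committee in section 3.3, and section 2.9 refers to Appendix E for the data-collection time points. Neither section 3.3 nor the Appendix E figure is available, and a harms procedure could be in either. This stands. The point applies to the text shown, and a reader should not conclude that the trial has no safety procedure.

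Second, a reader might infer that harms cannot be compared between arms at all. The documents do not support that. Residual-limb and phantom pain, depressive symptoms and function are measured at T1 to T3 in both arms, assessors are blinded to allocation, and care encounters are collected without restriction by arm. CES-D bears on the altered emotional status that section 1.5 also mentions. Nor are the reporting routes purely arm-specific, because the coordinators serve everyone.

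Third, a reader might expect SMART to show more events simply because it has more contact. That does not follow, for the reasons in step 4 of the working.

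Fourth, section 1.5 speaks of exploring issues. None of the research questions or hypotheses concerns harms, no between-arm harms analysis is stated, and the T3 interview covers part of the exploration. This lowers the weight of the point but does not remove it. The interview reaches 20 SMART participants and no controls, so it cannot show what happens without the programme.

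**Conclusion.** The point holds for over-exertion and residual-limb skin breakdown, and by extension for falls. In the text shown, none of the three has a scheduled, identical question in both arms, and the spontaneous routes differ in intensity and type. Between-arm counts of these events would be open to differential ascertainment, of unknown size and uncertain direction. Any risk ratio put on it would rest only on assumed capture rates, so none is given. The conclusion assumes that section 3.3 and the Appendix E figure do not already provide such questions. This is an inexpensive improvement to a stated purpose of the trial. It does not affect the validity of the primary analysis or of the scheduled secondary outcomes.

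**What to change.** First check whether section 3 already specifies scheduled harms questions for both arms. If it does, a cross-reference from section 1.5 is enough.

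If it does not, add the same short items to the existing T2 and T3 Qualtrics surveys in both arms: falls, residual-limb skin breakdown and over-exertion, each as yes or no with the number since the last visit. Define each term in the survey so that both arms answer the same question. State that these items, reported descriptively by arm, are the comparative data for these harms. Tabulate spontaneous reports separately, by arm and by route.

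The cost is about one minute per participant at each of two visits that already take place. Two limits remain and should be stated. The items are self-reported by participants who know their allocation, and SMART teaching may still affect what they recognise. Power for any formal test is also low. The change concerns measurement only and leaves clinical management as it is.
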